|                               |                                                                                                                                                                                                                 |
|-------------------------------|-----------------------------------------------------------------------------------------------------------------------------------------------------------------------------------------------------------------|
| Protocol Title         | Effects of a Physical-Psychological Integrative (PPI) Intervention on Physical Inactivity, Depression and Chronic Pain for Community-Dwelling Spinal Cord Injury Survivors: A Pilot Randomized Controlled Trial |
| Principal Investigator | [name]                                                                                                                                                                                                          |

a) Introduction

Spinal cord injury (SCI) is a neurological disorder that leads to “partial or complete loss of people’s motor and/or sensory function below the level of the injury” [1]. A review of the epidemiology of worldwide SCI reported that the incidence lied between 13 and 163.4 per million people, and the global prevalence ranged from 490 to 526 per million among developed counties [2]. The “International Campaign for Cures of Spinal Cord Injury Paralysis” stated that a conservative estimation of the worldwide prevalence of people with SCI-caused paralysis is over 2.5 million [2]. In Hong Kong, there is no central registration for the exact number of SCI survivors. According to the information of Hospital Authority (<https://www.ha.org.hk/>) and non-government organization (<https://www.4limb.org/>), there are currently thousands of SCI survivors living in the community, and the total SCI population is increasing with around 200 new cases of traumatic spinal cord injuries every year in Hong Kong. Most of the new SCI cases result from car accidents, industrial accidents, or falls. Older adults are also prone to SCI as their degenerated spines are vulnerable to severe injury. Importantly, various SCI-related chronic conditions impose a huge economic burden (costs ranging from US\$ 68,000 to 180,000 per person per year) on the healthcare system [3].

Currently, there is no effective treatment to cure SCI, although the life expectancy of SCI survivors is now equivalent to the general population given the improvement in medical treatment. Patients often suffer immediate and

irrecoverable neurological loss and severe disabilities that last for the rest of their lives. Prior research has indicated that people with paraplegia/tetraplegia following traumatic SCI have a lower quality of life than the general Hong Kong population and they need more medical care, psychosocial support, and environment adaptation [4]. People with SCI experience various secondary physical and psychological consequences during the long recovery process. Physical inactivity, depression, and chronic pain are the major challenging problems and have detrimental effects on these people's quality of life and well-being. Approximately 50% of the SCI population have no engagement in leisure-time physical activities such as wheeling, therapeutic exercise, or equipment-assisted walking after they are discharged from inpatient rehabilitation, and this inactivity is linked with increased risk for depression, pain, and poor quality of life [5]. Physical inactivity is not only determined by people's levels of injury and severity at post-SCI but also related to their behavioural patterns and psychological conditions [6]. Those with more negative emotions and low levels of self-efficacy will have lower motivations and engagement in physical activities. Depression (caused by a variety of medical, psychological, and social factors) is the most common mood problem in people with SCI, and it interferes with the ability of individuals to engage in daily life activities and affects their life satisfaction [7]. The prevalence rate of depression at post-SCI ranges from 9.8% to 63.9% at post-SCI, which is significantly higher than those of non-SCI counterparts (5.3%-11.3%) [8]. Chronic pain (persisting for more than 12 weeks) also remains a significant problem at post-SCI, with an estimated prevalence rate of around 70%-80% during long-term rehabilitation [9]. Chronic pain has a significant negative impact on the physical and emotional functioning of people with SCI, and a strong interrelationship has been found between pain and depression among people with SCI [10].

A systematic review of 19 clinical trials of activity-based interventions for people with SCI has demonstrated positive effects on people's mobility, independence, and quality of life [6]. However, most of these trials were conducted in the inpatient rehabilitation or the sub-acute phase of post-SCI. Very few trials focused on the long-term rehabilitation outcomes of people with SCI living in the community, which might be due to the barriers of transportation and lack of face-to-face interaction with healthcare professionals. Two pilot trials that integrated physical activities (e.g., home-based aerobic exercise) and telephone counselling from physiotherapists indicated positive effects of an activity-based intervention on patients' functional improvement and physical fitness [11, 12]. In addition, previous research also indicated positive effects of physical activities on SCI survivors' mood (e.g., depression) and subjective well-being [12]. People's adherence to the practice of physical activities after community reintegration remains a big challenge and studies highlighted the importance of psychological intervention (i.e., motivational interviewing) in enhancing patients' motivation and adherence to physical activity [12]. Telephone counselling and online face-to-face meetings will be good modalities for overcoming the barriers of not having face-to-face interactions and problems of transportation.

Non-pharmacological interventions (e.g., psychological approaches) for the treatment of depression and pain at post-SCI are effective alternatives/adjunct therapies to pharmacological intervention which are associated with various side effects including constipation, toxicity, and/or increased addiction/abuse [13, 14]. Psychological interventions (e.g., cognitive behaviour therapies, mindfulness interventions) have been given much attention in recent research and have shown positive effects in relieving depression, pain intensity, and

pain-related disability of people with SCI [15, 16]. In addition, psychological interventions can enhance people's self-efficacy and confidence in facing various challenges and stressful situations at post-SCI, as well as improve engagement in physical exercise and rehabilitation [15]. Prior research showed two main waves of psychological interventions for people with SCI including cognitive behaviour therapies and coping skills-based interventions/training. The most recent focus (the third wave) is to apply acceptance- and mindfulness-based interventions, in order to cultivate 'acceptance' of thoughts, behaviours, and emotions [17]. A recent systematic review of five mindfulness interventions for people with SCI indicated a significant reduction in depressive symptoms and pain-related outcomes [17]. However, conclusions are preliminary given the small number of included studies and moderate-to-high risk of bias in these studies (e.g., small sample sizes or lack of a control group). That said, the current evidence highlights the potential for mindfulness interventions in improving outcomes (i.e., depression and chronic pain), and the need of more high-quality studies in this area.

In summary, there is a considerably large group of community-dwelling SCI survivors in Hong Kong who are having low quality of life [4]. Physical inactivity, depression, and chronic pain are major problems faced by SCI survivors discharged from the acute phase of treatment or inpatient rehabilitation. Psychological factors play pivotal roles in determining people's engagement in post-discharge physical activity, as well as the management of depression and chronic pain. There is a scarcity of research that has addressed both the physical and psychological needs of community-dwelling SCI survivors in Hong Kong. Further, people with SCI living in the community may have great difficulties in engaging in face-to-face group intervention due to their reduced physical function. Online interventions (e.g., video meetings by Zoom)

may be a good alternative for community-dwelling SCI survivors to overcome the physical barriers (i.e., transportation), and to enhance their adherence to interventions. Given the above, our team will be the first to develop an online-group intervention that includes both physical activity promotion and psychological approaches (i.e., mindfulness-based skills training and SCI-related psychoeducation) to address the health needs of community-dwelling SCI survivors in Hong Kong. Specifically, the physical activity component will address participants' rehabilitation needs by enhancing their physical activity and body functions, while the psychological component will promote their subjective well-being and community participation. The integration of the physical and psychological approaches can truly meet community-dwelling SCI survivors' needs [18], as well as fill the research gaps of lacking high-quality randomised controlled trials. Previously, our team has conducted group-based psychosocial interventions (i.e., coping-oriented supportive programme) for people with SCI during inpatient rehabilitation, and the programme resulted in significant improvement of participants' coping ability, mood, and life satisfaction [19, 20].

Taken together, the proposed intervention not only can potentially promote physical activities but lower the risk of depression and chronic pain in people with SCI. Proper management of these chronic conditions can further reduce medical costs and healthcare burdens. Our findings will lay the foundation for a fully powered randomized controlled trial which would be a reference for the policymakers to develop innovative and comprehensive community healthcare for people with SCI in Hong Kong. As such, this project can meet the service gaps by providing community health support for people with SCI in Hong Kong, who are highly vulnerable (and maybe marginalized) due to their severe life-long disability. It will also echo the Hong Kong Food and Health Bureau's

strategic direction to stepping up the control of modifiable risk factors (e.g., physical inactivity) for non-communicable diseases, as well as to support the Hong Kong Government's commitment to "fighting against non-communicable diseases on all fronts and alleviating its burden" [21].

b) Aims and Hypotheses to be Tested

This study **aims** to evaluate the feasibility, acceptability, and preliminary effects of an eight-week Physical-Psychological Integrative (PPI) online-group intervention on physical inactivity, depression, and chronic pain for people with SCI living in the community.

Research hypotheses: when compared with those the control group (online telephone didactic education), participants in the PPI intervention group will indicate significantly greater:

1. Improvements in *the minutes of performing the moderate-to-rigorous physical activity as well as the number of days they are physically active* for a total of at least 60 minutes or more per day at post-intervention, and 3-month follow-up;
2. Improvements *in depression and chronic pain* at post-intervention, and 3-month follow-up;
3. Improvements in *mindfulness skills and quality of life* at post-intervention, and 3-month follow-up.

c) Plan of investigation:

(i) Study method/design

An open-label, two-arm pilot RCT will be conducted to investigate the effects between the intervention (PPI online-group intervention) and the control group (brief online didactic education) for people with SCI living in the community over a 3-month follow-up. Qualitative interviews with focus groups involving participants in the PPI intervention group will be conducted post-intervention,

to explore participants' views about acceptance, strengths and limitations, and suggested improvements of the intervention. Participants' recruitment and other study procedures are summarized in a flow chart (Appendix 1) according to the CONSORT statement.

(ii) Participants (subjects)

Study participants will be recruited from the Hong Kong Direction Association for the Handicapped and other community centers in Hong Kong, where groups of people with physical impairments can be reached. The Hong Kong Direction Association for the Handicapped (<https://www.4limb.org/>) is a **typical non-government organization that serves a large group of people with severe physical impairment/handicaps in Hong Kong**. According to personal communication with the President of the Association, there are approximately a thousand members of the association and over 30% of them are SCI survivors. Emails/phone call invitations will be sent to potential participants and advertising posters will also be used to encourage them to participate.

Eligibility:

People with SCI will be included if they are: (1) at least 18 years old; (2) currently living in the community and having SCI for more than 6 months; (3) complete injury at the C6 or below or incomplete injury at any level; (4) having a computer/smartphone with audio-speaking function and Zoom software, and internet access in a secure place; (5) using a wheelchair for at least 2 hours a day and having approval from their physicians to perform exercises; (6) having no problems in hearing, verbal communication and vision; and (7) able to communicate in Cantonese and to provide informed consent.

People with SCI will be excluded if they are: (1) presenting with any significant cognitive impairment or brain injury; (2) engaged in ongoing psychotherapy or

any other physiotherapy/exercise/relaxation interventions; (3) physically active for more than 150 minutes per week; and (4) experiencing significant psychotic symptoms, substance misuse or medically unfit for the exercise and psychological programme as diagnosed by their physicians.

#### Sample size

As this proposed study is to develop and evaluate the feasibility, acceptability, and preliminary effectiveness of the PPI intervention, a widely acceptable sample size (i.e., 30 participants in each study group) for a preliminary analysis to examine intervention feasibility and to estimate a between-group effect will be adopted [22]. Considering a 20% attrition rate, 36 people with SCI per study group (i.e., 72 people in total) will be recruited. A purposive sampling by key informants (containing both participants who completed the whole intervention sessions and those who withdrew from the intervention period) will be conducted for focus-group interviews (i.e., 4-5 participants per group), until saturation of the information was reached.

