#### Randomization and masking

After the completion of the baseline assessment, eligible participants will be randomly allocated to two study groups. The random allocation will be conducted by an independent researcher with an external randomization service (i.e., sealedenvelope.com), using random permuted block sizes (i.e., 4 or 6) to ensure balanced group numbers. Participants will not be blinded due to the nature of the intervention. Participants will be reminded to keep the intervention content confidential and not discuss this with participants in the control group to avoid contamination. Assessor-blind is not adopted as measurements are self-reported. Assistance provided by caregivers and research assistants might be needed for those who have difficulties in filling out surveys.

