### Ethical considerations

Ethical approval will be obtained from the Hong Kong Polytechnic University. This study will be performed in accordance with the Helsinki Declaration. Written informed consent will be obtained from all participants before the baseline assessments of the study, and will also be obtained from purposely sampled participants prior to all focus-group interviews. Participation is entirely voluntary for people with SCI and they can withdraw from the research at any time without any penalty. Participants' identities and data (information

collected and videotape records) will be protected by maintaining anonymity and confidentiality. Only authorized personnel can access the data for analysis.

(iv) Data processing and analysis

Feasibility and acceptability

**The feasibility** assessment of subject recruitment and follow-up will include (1) time taken to recruit the target sample size; (2) recruitment rate: the number of eligible participants approached who agree to consent divided by all subjects eligible to participate; (3) retention rate: the number of participants who complete the study divided by all participants who agree to consent; (4) drop-out rate: the number of participants who dropped out after randomization divided by all participants who agree to consent; and (5) reasons for dropping out will be collected from participants who dropped out.

**The acceptability** of the intervention will be indicated by (1) adherence rate: the number of PPI intervention sessions practiced divided by the total number of required sessions; (2) adverse events record associated with PPI intervention; and (3) satisfaction: participants' satisfaction with the intervention will be assessed with the Client Satisfaction Questionnaire [25]. The acceptability of the intervention will also be assessed by focus-group interviews with a purposive sample of participants who completed the whole intervention sessions and those who withdrew from the intervention period. Participants' perspectives about the acceptability, strengths, and limitations of the study and suggestions on the improvements of the interventions will be explored.

Preliminary effectiveness

All participants will be assessed at pre-, post-intervention, and 3-month follow-up by the research assistant. A self-designed form will be used to collect data on participants' socio-demographics and medical history, including age, gender,

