## Data analysis

All quantitative data from the pre- and post-tests will be numerically coded, summarized (with descriptive statistics), and analyzed using IBM SPSS 26. Both intention-to-treat and per-protocol analyses will be performed. Effect sizes of between-group comparisons will be estimated using Cohen's *d* which is applicable for small sample sizes [29]. Comparison of baseline information between two study groups will be performed by t-test, Mann-Whitney U, and/or Chi-square tests depending on the nature of the data. The generalized estimating equation will be used to assess the changes in the outcome measurements between groups over time, followed by contrast tests. Co-variance (if any found in the baseline comparison) will be adjusted during the analysis of intervention effects. Subgroup analysis will be conducted for certain factors (e.g., complete and incomplete injury or intervention completion and non-completion). Level of significance is set at  $p < 0.05$  (2-tailed).

Focus group interview data will be content analyzed. Tape-recorded interviews will be transcribed into Cantonese by one research assistant and cross-checked by the other research assistant. Codes will be discussed and agreed between our team members, combined to form categories/subcategories, and explained with verbatim data. Any discrepancy in coding/category will be discussed and final themes/subthemes will be confirmed by our team.

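### The 20% attrition allowance is added to the 30 per group instead of being taken from those recruited, so 36 per group leaves 28.8 completers per group, not 30 (minor, wrong as written)

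*Protocol*

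**What the plan says.** The whole sample-size argument stands in the Sample size section of the protocol. It takes "a widely acceptable sample size (i.e., 30 participants in each study group) for a preliminary analysis", with a reference on pilot trials, and adds the attrition step: "Considering a 20% attrition rate, 36 people with SCI per study group (i.e., 72 people in total) will be recruited". No power, standard deviation or effect size enters these figures.

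Under Feasibility and acceptability, in part (iv) on data processing and analysis, the protocol defines the "drop-out rate: the number of participants who dropped out after randomization divided by all participants who agree to consent". The denominator is therefore those who enter the study, not those who remain at the end.

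Randomization and masking describes two groups allocated "using random permuted block sizes (i.e., 4 or 6) to ensure balanced group numbers", which fits equal groups of 36.

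**The concern.** The figure of 36 is there to protect the figure of 30 against a 20% loss, and it does not do so. Adding 20% to the target differs from allowing for a loss of 20% of those recruited, and the first always gives the smaller number.

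The consequence is mainly one of interpretation. This is a feasibility pilot in which retention and drop-out are themselves outcomes. If attrition came out exactly as assumed, the trial would still finish below the 30 per group that it names, and a reader could take that for a retention failure. The results are also meant to inform the sample size of a full trial, where the same step might be repeated with larger numbers.

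**Working it through.** **Inputs**

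- Target per group: n = 30 (Sample size).
- Attrition: a = 0.20 (Sample size).
- Recruited: 36 per group, 72 in total (Sample size).
- Denominator of drop-out: all who consent (Feasibility and acceptability).

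Two readings are assumed. The attrition rate in Sample size is taken to be the same kind of quantity as the drop-out rate defined later, and the 72 recruited are taken to be those who consent and are randomised.

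**1. Reproducing the stated figure**

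n x (1 + a) = 30 x 1.20 = 36 per group, and 2 x 36 = 72. This reproduces both stated figures exactly.

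**2. What 36 per group delivers at 20% attrition**

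36 x (1 - 0.20) = 28.8 per group, and 72 x 0.80 = 57.6 in total. The shortfall is 30 - 28.8 = 1.2 per group, or 2.4 in total.

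**3. Attrition at which 36 per group keeps 30**

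1 - 30/36 = 6/36 = 16.7%.

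**4. Allowance that keeps 30 in expectation**

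n / (1 - a) = 30 / 0.80 = 37.5, rounded up to 38 per group, or 76 in total. Check: 38 x 0.80 = 30.4, which is at least 30.

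**5. Chance of reaching 30 completers**

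Let the number of completers in an arm be binomial with retention probability 0.80, independent between participants and arms.

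| Recruited per arm | P(arm has at least 30) | P(arm has fewer than 30) | P(both arms have at least 30) |
|---|---|---|---|
| 36 | 0.401 | 0.599 | 0.401² = 0.161 |
| 38 | 0.655 | 0.345 | 0.655² = 0.429 |

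**6. Effect on precision**

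The approximate half-width of the 95% confidence interval for Cohen's d with m per group is 1.96 x √(2/m + d²/(4m)). At d = 0.5:

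- m = 30: 1.96 x √(0.06667 + 0.00208) = 0.514.
- m = 28.8: 1.96 x √(0.06944 + 0.00217) = 0.525.

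The ratio is √(30/28.8) = 1.02, a widening of about 2%.

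**The case against.** The other side has four arguments, and most of their substance stands as a limit on the consequence.

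- **The target is a convention.** Thirty per group is taken from general practice for pilots, and nothing was derived from it. Falling 1.2 per group short breaks no stated power or error rate. This stands, and it is why the point is minor. It does not make the step from 30 to 36 right.
- **Completers are not the same as participants analysed.** The Data analysis section plans both intention-to-treat and per-protocol analyses, with generalized estimating equations over time. Someone who leaves after the post-intervention assessment can still contribute data. A reader might infer that the trial needs 30 analysable participants per group and will not have them, but the protocol does not put it that way. The shortfall holds for completers. Those lost before any post-baseline assessment still add no outcome data.
- **No expected-value allowance guarantees the target.** A reader might take the 60% chance of an arm ending below 30 as the harm done by the error. With 38 per arm that chance is still 34%, and both arms reach 30 only 43% of the time. Only the difference between the two rows of the table belongs to the miscalculation. Independence is also an assumption, because the intervention is delivered in groups of 4 to 5 whose members may leave together.
- **The 20% could be meant as a share of the 30.** Then 36 would be correct. Nothing in the protocol says so, and its own definition of drop-out uses those who consent as the denominator. On that definition, losing 6 of 36 is 16.7%. This argument does not stand.

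**Conclusion.** The sentence is wrong as written, and the error is minor. With 20% attrition over those recruited, 36 per group leaves 28.8 completers per group (57.6 in total). The stated 30 survives only if attrition is 16.7% or less. No other section of the protocol corrects the figure.

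The result rests on the two readings given with the inputs. If some people consent but are not randomised, 20% of all who consent is a larger number than 20% of 72, and the shortfall grows.

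A reader might conclude that the trial is too small or must enrol 76. The documents do not support that: precision changes by about 2%, the target is a rule of thumb, and the aims of feasibility, acceptability and preliminary effect estimation can be met with about 29 completers per group.

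**What to change.** Reword the sentence in Sample size so that the figures agree, for example:

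> 36 per group (72 in total) will be recruited, leaving about 29 completers per group (58 in total) at 20% attrition; 30 per group is retained only if attrition is at most 16.7%.

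The cost is one sentence. Recruitment, analysis and procedures stay as they are. Recruiting 38 per group (76 in total, four more participants) would keep 30 in expectation at 20% attrition, but it is not needed to put the plan right.
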